#### Secondary outcome measurements

Body composition is one of the secondary outcomes of this trial. The body composition test assesses each participant’s weight, body fat mass, body mass index, percentage of body fat, and weight-to-hip ratio. The participant will stand barefoot on the Inbody body composition analyzer (Inbody 770; Inbody Co., Ltd., South Korea). After their weight has been measured, the participant will grasp the handles and the machine will pass multifrequency signals through their body to obtain the impedance corresponding to each frequency. Using these measured impedance values, the machine will calculate how much body fat they have. The test will be conducted at baseline (assessment 1), week 8 (assessment 3), and at the follow-up visit (assessment 4).

Heart rate is another secondary outcome of this trial. The heart rate of participants will assessed when they are in a stable state at the same time as their blood pressure is measured. Thus, measurements will be conducted at baseline (assessment 1), prior to each of the visits (assessments 2 and 3), and during the follow-up visit (assessment 4).

The intensity and difficulty of the exercises are also secondary outcomes. The aim is to compare their subjective assessment of the intensity of the exercise with its absolute intensity. The experimental group will be asked four questions.
Was this exercise routine easy to follow?Is taichi useful for improving your health?Was the taichi conducted at appropriate time for you?Is the reference book helpful for performing taichi on your own?

Participants will answer each question using a 0 to 10 category scale.

They will rate the difficulty of the taichi exercises using a 0 to 10 visual analog scale, on which 0 indicates no difficulty and 10 indicates the maximum possible difficulty the person can imagine. Both surveys will be conducted once at the end of the final taichi session. Thus, the measurement point will be week 8 (assessment 3).

### Sample size

This study took into account the results of a previous study [18] that used taichi as the main evaluation index. The calculated sample size necessary for the *t*-test was 36 subjects in each group, which was conducted with a G power analysis with an effect size of 0.67, test power of 0.80, and significance level of 0.05. Considering a dropout rate of 10%, we aim to recruit a total of 40 subjects in each group.

### Statistical analysis plan

Continuous variables will be expressed as mean ± standard deviation, and categorical variables will be expressed as *n* (%). The demographic baseline information (age, gender, occupation, past history, present illnesses, and medications) will be tested using the chi-squared test and independent *t*-test.

As the primary statistical analysis, the effectiveness of taichi will be tested by calculating the differences in the maximum SBP and minimum DBP before (baseline) and after (week 8) treatment for each test subject. Comparisons of the within-group differences will be performed using a paired *t*-test and between-group differences using an independent *t*-test. If the data do not have a normal distribution, they will be tested using a nonparametric test (a Wilcoxon signed-rank test or Wilcoxon rank-sum test).

The heart rate and the body composition of the participants will be tested to verify the effectiveness of taichi by calculating the difference between before (baseline) and after (week 8) the treatment as described above.

The results of the questions regarding the intensity and difficulty of the exercises will be evaluated by the researchers, and the numerical value will be analyzed by a simple descriptive statistical method. We will perform a simple correlation analysis or simple regression analysis to determine whether there is a correlation between the differences in blood pressure and the intensity and difficulty of the exercise as perceived by the experimental group.

Information regarding adverse events will be collected through patient reports and researchers’ observations. The frequency of adverse events will be analyzed by a chi-squared test or Fisher’s exact test.

All statistical analyses will be conducted in a two-sided manner, with a significance level of 5%. In addition, we will use an intention-to-treat analysis for missing data in the primary and secondary analyses. The last-observation-carried-forward and multiple imputation, which are widely used in clinical research, will be applied to missing data and additional multiple imputation or regression analysis will be used to check any differences.

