#### Primary outcome measurements

Blood pressure will be the primary outcome of this trial. The CRC will assess the participant’s blood pressure in a stable state using an automatic electronic blood pressure monitor (HBP-1300, Omron Dalian Co., Ltd., China). To obtain accurate data, the measurements will be conducted three times and their mean value will be used as the outcome. Blood pressure will be measured at baseline (assessment 1), prior to each of the visits (assessments 2 and 3), and during the follow-up visit (assessment 4). The primary endpoint is week 8 (assessment 3).

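### The primary outcome is defined as the mean of three blood pressure readings, but the primary analysis is written on the maximum systolic and minimum diastolic pressure, and nothing reconciles the two

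*Protocol article*

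**What the plan says.** Under *Primary outcome measurements*, the protocol article says of blood pressure that "the measurements will be conducted three times and their mean value will be used as the outcome", and it names week 8 (assessment 3) as the primary endpoint.

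Under *Statistical analysis plan*, the primary analysis tests the effect of taichi by "calculating the differences in the maximum SBP and minimum DBP before (baseline) and after (week 8) treatment for each test subject". Arms are compared on "between-group differences using an independent *t*-test", with a rank-sum test if the data are not normal, two-sided at 5%.

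No other section settles which variable is meant. The registration data set (Table 2) gives the primary outcome only as blood pressure. The *Sample size* section works from an "effect size of 0.67, test power of 0.80, and significance level of 0.05" without saying which blood pressure variable the effect size describes. The *Abbreviations* list expands SBP and DBP as systolic and diastolic pressure and defines neither *maximum* nor *minimum*.

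**The concern.** With three readings at a visit, the mean and the extremes differ for every patient whose readings are not identical. An analyst who follows the outcome section and one who follows the analysis section would therefore compute different primary variables from the same data.

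Two things are at stake. The first is which result counts as the prespecified one, because the article supports either variable. The second is precision. The largest or smallest of three readings is a less stable measure of a patient's pressure than their average, and the sample size leaves almost no spare power to absorb extra noise.

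**Working it through.** **1. The plan's own figure.** Inputs from *Sample size* and *Statistical analysis plan*: d = 0.67, power 0.80, two-sided alpha 0.05, 1:1 allocation.

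- Two-sample t-test (noncentral t): n = 35.96, so 36 per group. This agrees with "The calculated sample size necessary for the *t*-test was 36 subjects in each group".
- Power at exactly 36 per group is 0.8005.
- Dropout: 36 / (1 − 0.10) = 40. This agrees with "Considering a dropout rate of 10%, we aim to recruit a total of 40 subjects in each group".

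The sample size arithmetic is sound, and it has no margin at 36 evaluable patients per group.

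**2. Mean against extreme of three readings.** Let s be the SD of a single reading around the patient's level at that visit. Assume three independent normal readings.

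- Variance of the mean: s²/3 = 0.333 s².
- Variance of the maximum, and equally of the minimum: 0.559 s² (simulation with 4 million draws gave 0.559).
- Ratio: 0.559 / 0.333 = 1.68.
- Expected position: the maximum lies about 0.85 s above the patient's level and the minimum about 0.85 s below it.

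**3. Effect on power if the extremes are analysed.** Let D be the SD of the change from baseline to week 8 when the mean of three readings is used. Two visits enter the change, so

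variance of change with the extreme = D² + 2 s² (0.559 − 0.333) = D² + 0.452 s².

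With the treatment difference in mmHg unchanged, and 0.67 taken to refer to the mean of three readings,

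d' = 0.67 × D / √(D² + 0.452 s²).

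The article gives neither D nor s. The ranges below are assumptions.

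| D (mmHg) | s (mmHg) | SD with extreme | d' | Power at 36 per group | n per group for 80% |
|---|---|---|---|---|---|
| 15 | 3 | 15.14 | 0.664 | 0.793 | 37 |
| 10 | 5 | 10.55 | 0.635 | 0.757 | 40 |
| 8 | 8 | 9.64 | 0.556 | 0.643 | 52 |

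Middle row: 100 + 0.452 × 25 = 111.3; √111.3 = 10.55; 0.67 × 10 / 10.55 = 0.635. In that case 40 evaluable patients per group are needed, which is the whole recruitment target with nothing left for dropout.

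The mathematical limit, with all variance of the change coming from reading error, is d' = 0.67 × √(0.333/0.559) = 0.517, with power 0.58 and n = 60 per group.

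**4. Effect on bias.** For the maximum, the expected change in an arm is the true change plus 0.85 × (s at week 8 − s at baseline). If s is the same at both visits, the extra term is zero. If s moves equally in both arms, it cancels between them. A residual remains only if within-visit variability comes to differ by arm. It would be about 0.85 mmHg per 1 mmHg of arm difference in s at week 8, with opposite signs for SBP and DBP.

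**5. If the mean is used in both places.** Nothing in step 1 changes: 36 per group, 40 with dropout, power 0.80.

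**The case against.** The strongest reply is that the literal reading is not what the authors meant. Systolic pressure is the maximum of the pressure cycle and diastolic the minimum, so the two words may be redundant labels. The analysis section never says that the extremes are taken over the three readings. The outcome section, by contrast, is explicit that three readings are averaged, and it gives accuracy as the reason. Nothing in the article explains why anyone would then want the highest systolic and lowest diastolic value. This is a fair reading, and under it the loss of precision disappears.

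It is still an inference. The words are attached to SBP and DBP, which already mean systolic and diastolic, and they appear only in the sentence that defines the primary test. The inconsistency stands under either reading; its consequence does not.

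Three stronger readings are tempting, and the article does not support them:

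- A reader might infer a bias of several mmHg from the shift of 0.85 s (4.2 mmHg if s were 5). That is a shift in level at one visit. The plan tests change between arms, where the shift largely cancels. No section gives evidence that taichi alters within-visit variability.
- A reader might take the 68% rise in variance as a rise in the variance of the primary endpoint. It applies to reading error alone. Variation between patients and between visits dilutes it, at the low end to a loss of about one point of power.
- A reader might infer that the variable will be picked after the results are seen. The *Blinding* section keeps the data analyst blind to allocation, expressly against selective reporting, and an analysis plan that is not shown may fix the variable. Blinding limits choice by result, but it does not say which variable is primary.

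**Conclusion.** The point holds as an unresolved inconsistency in the definition of the primary variable. That part rests on the text alone.

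The statistical cost is conditional. If *maximum* and *minimum* are followed literally as extremes of the three readings, reading-error variance is about 1.68 times that of the mean, and power at 36 per group falls from 0.80 to somewhere between 0.64 and 0.79. This assumes independent normal readings, an unchanged difference in mmHg, an effect size that refers to the mean of three readings, and SDs that the article does not give. If the words are only labels, there is no precision loss and a wording correction is enough. The article does not show which reading was intended. No bias in the treatment comparison and no error in the sample size is established.

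**What to change.** In *Statistical analysis plan*, state that the primary analysis uses the change from baseline to week 8 in the mean of the three readings, separately for SBP and for DBP, and delete *maximum* and *minimum*. This brings the section into line with *Primary outcome measurements*.

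The cost is one sentence, made before the data are analysed. It needs no new measurements and no change to the sample size. If extremes were really intended, they would have to be defined, the outcome section changed to match, and the sample size justified for that variable.

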In this study, we analyze the blood pressure, heart rate, and body composition of grade 1 hypertension patients who have been diagnosed during a medical examination in a hospital or had an SBP of 140–159 mmHg or DBP of 90–99 mmHg in a screening test. We will evaluate the effectiveness of taichi by comparing the control of hypertension in a group practicing usual care with that in an experimental group practicing usual care plus taichi. The effectiveness of taichi for hypertension will, thus, be assessed in this randomized, active-controlled, assessor-blinded, two parallel-armed trial.

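### The primary analysis leaves baseline blood pressure unadjusted, lists within-arm paired tests as evidence of effectiveness, and lets the data's distribution choose the test; one prespecified ANCOVA would be better at no cost

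*Protocol article*

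**What the plan says.** The Statistical analysis plan section of the protocol article bases the primary analysis on "calculating the differences in the maximum SBP and minimum DBP before (baseline) and after (week 8) treatment for each test subject". Three rules follow:

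- Within arms: "Comparisons of the within-group differences will be performed using a paired" *t*-test.
- Between arms: "and between-group differences using an independent" *t*-test.
- Choice of test: "If the data do not have a normal distribution, they will be tested using a nonparametric test", namely Wilcoxon signed-rank or rank-sum. No criterion for non-normality is given.

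Heart rate and body composition are handled the same way. Baseline blood pressure is not a covariate in any analysis described.

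On entry, the Background says that patients may have been diagnosed already or may have "had an SBP of 140–159 mmHg or DBP of 90–99 mmHg in a screening test"; the inclusion criteria give the same alternatives. Table 1 schedules vital signs before treatment only at screening (week 0). The Intervention section gives both arms education on salt, weight, alcohol, exercise and diet.

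The Sample size section uses "an effect size of 0.67, test power of 0.80, and significance level of 0.05" for a *t*-test, and the result "was 36 subjects in each group" is raised to 40 for 10% dropout.

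**The concern.** Three features of one paragraph need attention.

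1. **Paired tests.** They stand beside the between-arm test under the stated primary test of effectiveness, and the paragraph does not say which comparison decides. If the reading that admits a patient is also the baseline, it is selected to be high and the next reading falls on average with no treatment. Lifestyle education in both arms adds to the fall. A significant drop in the taichi arm could then be reported as a taichi effect.
2. **No baseline adjustment.** Baseline enters only by subtraction. With about 36 per arm some imbalance is likely by chance, and a change score over-corrects for it whenever the slope of week 8 on baseline is below 1. Some precision is also lost.
3. **Normality switch.** The primary test stays open until the data are seen, and the question can move from a difference in means to a comparison of ranks. At 36–40 per arm a *t*-test or ANCOVA tolerates moderate non-normality.

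**Working it through.** **Planned sample size.** For a two-sample *t*-test with d = 0.67, two-sided 5%, power 0.80 and 1:1 allocation, the noncentral *t* gives 35.96, so 36 per arm, with power 80.05% at 36. 36/0.90 = 40. The plan's figures reproduce.

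**Assumptions.** The protocol gives no population mean, SD or between-visit correlation, so all of these are assumed:

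- Unselected SBP has mean μ = 125 or 130 with SD σ = 16, or mean 138 with SD 12.
- The SD is the same at both visits, and the between-visit correlation is r. Then r is also the slope of week 8 on baseline, and selection on baseline leaves it unchanged.
- Entry is either on SBP alone (140 to below 160), or on SBP or DBP (90 to below 100) with nobody above either limit. For the second, DBP has mean 80, SD 10, correlation 0.6 with SBP, and adds nothing to predicting week-8 SBP beyond baseline SBP.

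**Precision.** Let v be the variance of baseline SBP among those who enter.

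- Change-score variance = (1−r)²v + σ²(1−r²).
- ANCOVA variance = σ²(1−r²).
- Ratio = (1+r) / [(1+r) + (1−r)v/σ²].

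Power uses d = 0.67 in change-SD units, divided by √ratio, on 69 df at 36 per arm.

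| Entry | μ, σ | v/σ² | r | Ratio | Power, ANCOVA |
|---|---|---|---|---|---|
| SBP | 125, 16 | 0.105 | 0.8 | 1.8/1.821 = 0.988 | 80.5% |
| SBP | 125, 16 | 0.105 | 0.6 | 1.6/1.642 = 0.974 | 81.0% |
| SBP or DBP | 125, 16 | 0.435 | 0.8 | 1.8/1.887 = 0.954 | 81.9% |
| SBP or DBP | 125, 16 | 0.435 | 0.6 | 1.6/1.774 = 0.902 | 83.9% |
| SBP or DBP | 125, 16 | 0.435 | 0.4 | 1.4/1.661 = 0.843 | 86.3% |

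The variance reduction is therefore about 1–16%.

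**Chance imbalance.** At 36 per arm the SD of the baseline difference is √(2/36) = 0.24 baseline SD. The change-score contrast keeps (1−r) times any imbalance. With baseline SD 5.2 to 10.6 mmHg and r = 0.6, one SD of imbalance shifts the estimate by 0.4 × 0.236 × 5.2 = 0.5 to 0.4 × 0.236 × 10.6 = 1.0 mmHg.

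**Between-arm error under no effect.** In 4,000 simulated trials at each of r = 0.4, 0.6 and 0.8 (μ = 138, σ = 12, SBP entry), the change-score *t*-test rejected in 4.9%, 5.1% and 4.9%, and ANCOVA in 4.6%, 5.2% and 5.0%.

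**Paired test with no effect of any kind.** Expected fall = (1−r)(m−μ), where m is the mean baseline of those who enter. The test has 36 patients and 35 df.

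| Entry | μ, σ | m | r | Fall (mmHg) | SD of change | Significant |
|---|---|---|---|---|---|---|
| SBP | 125, 16 | 147.1 | 0.6 | 0.4 × 22.1 = 8.8 | 13.0 | 98% |
| SBP | 130, 16 | 147.6 | 0.8 | 0.2 × 17.6 = 3.5 | 9.7 | 57% |
| SBP | 138, 12 | 147.6 | 0.6 | 0.4 × 9.6 = 3.8 | 9.8 | 62% |
| SBP | 138, 12 | 147.6 | 0.8 | 0.2 × 9.6 = 1.9 | 7.3 | 34% |
| SBP or DBP | 138, 12 | 146.5 | 0.8 | 0.2 × 8.5 = 1.7 | 7.3 | 28% |

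The nominal rate is 5%. Any effect of the education would add to these falls.

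**The case against.** The plan is consistent with itself: a *t*-test is planned, the sample size is for a *t*-test, and the numbers agree. Regression to the mean is expected equally in both randomised arms and cancels in their difference. The Background defines effectiveness by comparing the groups, and nothing says that a within-arm fall will be taken as proof. A normality criterion is a detail that a full analysis plan may hold. All of this stands, and it limits the point to interpretation, modest efficiency and fixing the primary test in advance.

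Three stronger readings are tempting and not supported.

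- *The between-arm test is biased.* It is not: its error rate is about 5%. Chance imbalance distorts a given trial's estimate but does not bias it over randomisation.
- *ANCOVA would save a quarter or more of the patients.* The familiar ratio (1+r)/2 would give 0.65 at r = 0.3 and 0.75 at r = 0.5, hence 24–28 per arm or power of 90–94%. That ratio needs equal variances at baseline and week 8. Entry on a blood pressure range narrows the baseline (SD about 5 against 10–13 at week 8 under SBP entry with σ = 16), and the gain shrinks to the figures shown. For the same reason the low correlation inside the window does not make change scores worse than ignoring baseline. What matters is the slope, and at slopes of 0.6–0.8 they do better.
- *The switch inflates type I error.* No inflation has been shown. The objection is that the test and the quantity estimated are left open.

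The two effects also pull against each other. Tight selection on SBP makes the untreated fall large and the ANCOVA gain small. Entry on DBP or a prior diagnosis tends to do the reverse. The largest values of both should not be claimed together.

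**Conclusion.** The point holds as a recommendation. The randomised comparison is valid and the sample size is correct for it. ANCOVA would remove the effect of chance baseline imbalance and reduce the variance by about 1–16% under the assumed populations (r 0.4–0.8), taking power from 80% to about 80.5–86% at 36 per arm. The true gain is unknown because the protocol gives no correlation.

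The firmer part is that the paired tests cannot show effectiveness. For r of 0.6–0.8, an arm with no effect would fall by about 2–9 mmHg and be significant in roughly 28–98% of trials. This rests on the assumed populations and on the screening reading serving as baseline, which Table 1 suggests but does not state. Patients who enter on a prior diagnosis were not modelled and may regress less. The shared education is a further reason, independent of these assumptions, why a within-arm fall cannot be credited to taichi.

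**What to change.** - Make the sole primary test the between-arm difference in week-8 blood pressure from ANCOVA with arm and baseline blood pressure in the model, each pressure adjusted for its own baseline. Report the adjusted difference with its 95% confidence interval.
- Use the same model for heart rate and body composition.
- Remove the paired tests from the test of effectiveness and report within-arm changes descriptively.
- Replace the normality switch with this one prespecified method, and keep the rank test as a sensitivity analysis.

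The cost is analysis wording only. Baseline values are already collected, and no patients or visits are added. The planned 36/40 per arm can stand.

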## Methods/design

### Study design

The proposed study is a randomized, active-controlled, assessor-blinded, two parallel-armed trial. It will be conducted at Pusan National University Korean Medicine Hospital (PNUKH) in Yangsan, Korea. The study protocol was approved by the institutional review board (IRB) of PNUKH on 16 January 2019 (approval number 2018014) and was registered in the Clinical Research Information Service on 18 March 2019 (KCT0003632). Table 1 is the schedule of enrollment, intervention, and assessments. Table 2 lists all relevant items in the World Health Organization’s trial registration data set.

**Table 1 Tab1:** Schedule of enrollment, intervention, and assessments

Measure	Screening (week 0)	Active treatment								Follow-up (12 weeks after screening)^†^
		Week 1	Week 2	Week 3	Week 4 (visit 1)^†^	Week 5	Week 6	Week 7	Week 8 (visit 2)^†^	
Study agreement	X									
Check for participation in other clinical trials	X									
Sociodemographic characteristics^1^	X									
Taichi exercises		Two sessions per week								
Body composition test	X								X	X
Measurement of vital signs^2^	X				X				X	X
Intensity and difficulty of exercises									X	
Number of taichi sessions attended										X
Adverse events					X				X	X

† ±3 days

^1^Age, gender, occupation, past history, present illness, and medications

^2^Blood pressure (systolic and diastolic), heart rate, and body temperature

**Table 2 Tab2:** All relevant items in the World Health Organization’s trial registration data set

Data category	Information
Primary registry and trial identifying number	Clinical Research Information Service, KCT0003632
Date of registration in primary registry	18 March 2019
Secondary identifying numbers	Not applicable
Source(s) of monetary or material support	Traditional Korea Medicine R&D program of Korea Health Industry Development Institute
Primary sponsor	Woosuk University
Secondary sponsor(s)	Not applicable
Contact for public queries	[name], [name], [contact]
Contact for scientific queries	[name], Department of Rehabilitation Medicine of Korean Medicine, Spine and Joint Center, Pusan National University Korean Medicine Hospital, [name].
Public title	Effects of taichi on grade 1 hypertension: A study protocol for a randomized controlled trial
Scientific title	The Effects of Taichi on Grade 1 Hypertension: Randomized controlled trial

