### Intervention

At their first visit, patients in both groups will be educated in managing their own blood pressure by restricting salt intake, losing weight, moderating alcohol consumption, exercising, and regulating their diet. Additionally, patients in both groups will be asked not to do any intense exercise that could influence the results of the trial. After this education, the usual care group will self-manage their own blood pressure for 8 weeks.

In addition to self-management, the experimental group will perform taichi as the study intervention. The taichi used in this study is Chen-style 18-form taichi, which will be conducted over two 60-min sessions per week for a total of 8 weeks (80% compliance and more than 13 sessions in total). In each session, patients will perform 10 min of warm-up exercises, 40 min of taichi, and 10 min of cool-down exercises. To maximize adherence to the study protocol, the intervention will mostly be performed in the 6th floor ward at PNUKH. If group sessions are needed, the practitioners can visit external locations. The patients in the experimental group will receive a reference book on taichi that will promote their retention of the exercises. A daily log will record how many exercises each patient has conducted. At weeks 4 and 8, both groups will visit the hospital for an assessment. After treatment, both groups will be monitored for an additional 4 weeks of follow-up.

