### Safety

Because the intervention is a simple exercise rather than untested drugs or medical devices, we do not expect any adverse events will be caused by the general Korean medical treatment. However, the investigators will inform the participants of all possible adverse events that may occur after taichi and instruct them to report any such adverse events. All adverse events recorded during the research period will be analyzed and reported. In general, due to the interventional characteristics of exercise, simple muscular pain may occur. We will provide beverages such as bottled water or green tea during the exercise sessions for the participants. To prevent falls and severe muscle aches, a chair will be available during exercise sessions. There will also be a space where participants can sit and relax. If a direct injury occurs in connection with this study, appropriate medical action may be taken, as determined by the investigator.

A data monitoring committee (DMC) comprising members of staff from the clinical research service institution (Woosuk University) will periodically monitor the study by telephone, e-mail, and visits, if necessary. The DMC will be composed of one statistician and one specialist in clinical research methodology. They will review the progress of the study and check all case report forms. In addition, they will check whether the study has followed the study protocol. If a problem is identified, the DMC will modify the protocol if necessary. If modifications to the protocol are required during the study, the modified protocol will be submitted by the clinical trial review committee to the IRB for approval. However, neither auditing nor an interim analysis are planned during the trial.

Additionally, as we will not collect any biological samples and do not intend to use the participants’ data in future studies, we do not need any additional consent for collection and use of participant data or biological specimens in ancillary studies. In accordance with government regulations and standards, all documents related to the conduct of a clinical trial must be kept by the director of clinical research, or the director of the institution and the clinical research manager, for at least 3 years after the completion of the clinical trial.

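### The between-arm adverse event test is at risk of unequal ascertainment, because it takes all recorded events while staff contact and the reporting instruction favour the taichi arm

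*Protocol article*

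**What the plan says.** Under Statistical analysis plan, the article names the sources, "Information regarding adverse events will be collected through patient reports and researchers’ observations", and then the test, "The frequency of adverse events will be analyzed by a chi-squared test" or Fisher's exact test. All tests are two-sided at 5%. With two arms, this is naturally read as a comparison between them. The Safety section adds that every adverse event recorded during the study will be analysed and reported, and Outcome assessment says that all of them are recorded.

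The Intervention section has taichi "conducted over two 60-min sessions per week for a total of 8 weeks", while "the usual care group will self-manage their own blood pressure for 8 weeks". Both groups attend at weeks 4 and 8 and are followed for four more weeks. Table 1 marks adverse events at week 4, week 8 and follow-up, with no distinction by arm. It also lists "Number of taichi sessions attended", so the taichi arm's attendance will be known.

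The one reporting instruction to participants is in the Safety section, where investigators will "inform the participants of all possible adverse events that may occur after taichi and instruct them to report any such adverse events".

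**The concern.** A between-arm comparison of adverse events is fair only if an event has about the same chance of being recorded in either arm. Three features of the plan pull against that:

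- Researchers' observations are a named source, and researchers have many more occasions to observe taichi participants.
- Participants are asked to report events tied to taichi, which gives a usual-care participant less reason to volunteer anything.
- The test takes every recorded event, so anything noted at a session counts in one arm and has no counterpart in the other.

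The one event the Safety section expects is mild muscle soreness. That is easily noticed or mentioned at a session and easily forgotten by a visit four weeks later. A significant excess under taichi could then reflect harm, closer observation or both, and the planned analysis could not separate them.

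**Working it through.** **The plan's own figures.** The article gives no figure for the adverse event test. The arm size used below comes from Sample size (effect size 0.67, power 0.80, two-sided 5%). The noncentral t distribution gives power 0.789 at 35 per arm and 0.8005 at 36, so 36 reproduces. With 10% dropout, 36 / 0.9 = 40, which also reproduces. That calculation concerns blood pressure and says nothing about adverse events.

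**Contacts after randomization.**
- Common visits in each arm (Table 1): week 4, week 8, follow-up = 3.
- Taichi sessions (Intervention): 2 x 8 = 16.
- Taichi at full attendance: 16 + 3 = 19, against 3 in usual care.
- Taichi at 13 sessions, about the stated compliance level (0.80 x 16 = 12.8): 13 + 3 = 16, against 3.

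These are occasions on which an event could come to staff attention. Scheduled adverse event collections are 3 against 3.

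**Effect of unequal detection.** The article gives neither an event risk nor a detection rate, so both are assumed. Let r be the true proportion of patients with at least one event, equal in both arms, and d the share of those patients detected. The observed proportion is p = r x d. With n = 40 per arm, the false-positive rate is the sum, over all pairs of counts (i, j), of Bin(i; 40, p1) x Bin(j; 40, p2) wherever the test gives P < 0.05. The chi-squared test is uncorrected. Detection in taichi is set at 90% throughout.

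| True risk | Usual-care detection | Observed, taichi v usual care | Fisher | Chi-squared |
|---|---|---|---|---|
| 10% | 90% | 9% v 9% | 1.4% | 5.9% |
| 10% | 70% | 9% v 7% | 1.6% | 7.1% |
| 10% | 50% | 9% v 5% | 2.8% | 11.5% |
| 20% | 90% | 18% v 18% | 2.8% | 5.2% |
| 20% | 70% | 18% v 14% | 4.4% | 8.0% |
| 20% | 50% | 18% v 10% | 11.0% | 18.4% |
| 40% | 90% | 36% v 36% | 2.8% | 4.9% |
| 40% | 70% | 36% v 28% | 7.7% | 11.6% |
| 40% | 50% | 36% v 20% | 27.5% | 35.5% |

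With equal detection, Fisher's test is conservative and chi-squared is close to 5%. At 10% risk with 90% v 50% detection, the expected event count per arm is 40 x (0.09 + 0.05) / 2 = 2.8. That is below 5, so Fisher's test would normally be used, and its rate stays under 5%. At 20% risk with 90% v 70%, Fisher's test also stays under 5%. The excess becomes material when events are common and the detection gap is wide.

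**The case against.** The strongest reply is that scheduled collection is equal. Table 1 has the same three adverse event collections in both arms, and the article says that all events are recorded. The sentence in the Safety section may be no more than loosely worded risk information. Nowhere does the article say that events are asked about or logged at sessions. The daily log counts exercises done, and researchers' observations could mean those made at the visits. The detection rates are assumptions, and under some of them there is no excess error with Fisher's test. Some true excess of muscle soreness under taichi is to be expected anyway, and more contact in the active arm is inherent in comparing exercise with usual care.

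Much of this stands. A reader might infer that events are prompted only in the taichi arm, or that the comparison is already shown to be biased and measures contact time instead of harm. Table 1 rules out the first reading. The second would need session logging and detection rates that the article does not give. Nor does the article set any hypothesis of fewer adverse events under taichi that under-counting in usual care could defeat.

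What the reply does not remove is the risk. Staff presence at sessions is a reasonable inference: there are trained taichi educators, most sessions are in a hospital ward, practitioners may travel to group sessions, and provision is made against falls. An event seen there must be recorded under the record-everything rule, and nothing keeps it out of the test. That rule widens capture where contact is greater and does not equalize it. An article may leave the wording of a case report form to the full protocol, but here it states the sources, the test and the instruction itself.

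**Conclusion.** The point holds as a risk of unequal ascertainment, not as demonstrated bias. Choosing chi-squared or Fisher's test is not the error; the weakness lies in which events enter the test and how participants are asked to report.

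The size is unknown. On the assumptions above (equal true risk, 40 per arm, 90% detection in taichi), the false-positive rate ranges from no excess over 5% with Fisher's test, when events are rare or the detection gap modest, to 27.5% (Fisher) or 35.5% (chi-squared) at 40% true risk with 90% v 50% detection. No row of that range can be preferred from the article.

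The point is minor. Adverse events are neither the primary nor a listed secondary outcome, and the blood pressure conclusions are unaffected.

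**What to change.** Three changes of wording:

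1. In Safety, instruct participants in both arms to report any adverse event, whatever its cause.
2. In Statistical analysis plan, base the between-arm comparison on the number of patients with at least one adverse event collected in the same way in both arms at the week 4, week 8 and follow-up visits.
3. Report events noted only at taichi sessions descriptively for that arm, for example per session attended, and give the comparison of all recorded events as a sensitivity analysis.

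No visit is added, since Table 1 already schedules these collections. The article describes a trial still recruiting. The instruction can change for participants and visits still to come, and the analysis rule can be fixed before allocation is revealed to the analyst.

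The cost is that session-only events leave the main test, which then relies on recall over about four weeks in both arms. Those events are still reported. Equal collection also does not remove every difference, because participants know their allocation and sessions may sharpen recall at a visit. The result should still be read with that in mind.
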